# Comparison of a standard CO_2_ pressure pneumoperitoneum insufflator versus AirSeal™: study protocol of a randomized controlled trial

**DOI:** 10.1186/1745-6215-15-239

**Published:** 2014-06-20

**Keywords:** Pneumoperitoneum, AirSeal™, Laparoscopy, CO_2_ Insufflator, Shoulder pain

## Abstract

**Background:**

AirSeal™ is a novel class of valve-free insufflation system that enables a stable pneumoperitoneum with continuous smoke evacuation and carbon dioxide (CO_2_) recirculation during laparoscopic surgery. Comparison data to standard CO_2_ pressure pneumoperitoneum insufflators is scarce. The aim of this study is to evaluate the potential advantages of AirSeal™ compared to a standard CO_2_ insufflator.

**Methods/Design:**

This is a single center randomized controlled trial comparing elective laparoscopic cholecystectomy, colorectal surgery and hernia repair with AirSeal™ (group A) versus a standard CO_2_ pressure insufflator (group S). Patients are randomized using a web-based central randomization and registration system. Primary outcome measures will be operative time and level of postoperative shoulder pain by using the visual analog score (VAS). Secondary outcomes include the evaluation of immunological values through blood tests, anesthesiological parameters, surgical side effects and length of hospital stay. Taking into account an expected dropout rate of 5%, the total number of patients is 182 (n = 91 per group). All tests will be two-sided with a confidence level of 95% (*P* <0.05).

**Discussion:**

The duration of an operation is an important factor in reducing the patient’s exposure to CO_2_ pneumoperitoneum and its adverse consequences. This trial will help to evaluate if the announced advantages of AirSeal™, such as clear sight of the operative site and an exceptionally stable working environment, will facilitate the course of selected procedures and influence operation time and patients clinical outcome.

**Trial registration:**

ClinicalTrials.gov NCT01740011, registered 23 November 2012.

## Background

Laparoscopic surgery is currently actively used in a variety of surgical conditions and is performed through the creation of a workspace between the abdominal wall and the internal organs, most commonly by the insufflation of carbon dioxide (CO_2_) to the level of positive intra-abdominal pressure tolerated by the patient. CO_2_ is the most frequent employed medium because it is relatively inexpensive, colorless, odorless, nonflammable and rapidly eliminated from systemic circulation [1,2]. A good exposure to the operative field facilitates an improved technical performance and is a factor that affects the duration of an operation and the safety of a patient during the course of the procedure. Conventional CO_2_ insufflation systems often respond with a delay to increased intraoperative pressure loss. The collapse of the abdominal cavity during increased systemic absorption of CO_2_ gas, for example as a result of suction or smoke evacuation, may prolong operation time and can be prevented only by an increase in CO_2_ insufflation pressure. The CO_2_ and higher abdominal pressure adversely affects the patient’s homeostasis, causing significant changes in cardiovascular and respiratory systems, decreasing perfusion in abdominal organs and blood flow in the inferior vena cava and causing an increased risk of thrombotic disease [3].

Insufflation of CO_2_ during laparoscopic surgery leads to postoperative shoulder pain. The origin of shoulder pain is commonly assumed to be due to the overstretching of the diaphragmatic muscle fibres owing to a high CO_2_ pressure [4]. The physiology of the pneumoperitoneum is complex with local and systemic effects of a gas instilled under pressure [5]. It has been proven that surgical trauma is connected with the changes in cytokine concentration. Excessive production of pro-inflammatory cytokines after surgical procedures may have an unfavorable influence on the healing process and cause complication during postoperative period. Many physiological changes of laparoscopic surgery have recently been reported in research articles [6-8]. Among these studies, it has been theorized that conventional laparoscopic surgery under CO_2_ gas is immunologically superior to laparotomy [9]. Substantial experimental and clinical evidence also exists indicating that the immune response is better preserved after laparoscopic surgery [9-14], but the mechanism for immune system preservation under the CO_2_ gas-specific effect is still unclear in all situations. To examine changes in the concentrations of certain cytokines and angiogenic factors serum levels in the early postoperative period after laparoscopic surgery further studies are needed. Additionally, the absorption of CO_2_ during pneumoperitoneum can lead to an increase in PaCO_2_ level, however hypercapnia is commonly avoided by appropriate ventilatory changes. Absorption of CO_2_ also alters the acid–base balance and the increase in CO_2_ excretion load. Compared with baseline values, the increased intra-abdominal pressure during pneumoperitoneum can reduce femoral venous flow, intraoperative urine output, portal venous flow, respiratory compliance and cardiac output [3].

Recently, with AirSeal™, a novel class of valve and membrane-free insufflation and/or trocar system is available that responds immediately to the slightest changes in intra-abdominal pressure, maintaining a stable pneumoperitoneum and continuous smoke evacuation even under difficult surgical conditions and constant suction, ensuring visibility. This insufflation system is associated with reduced CO_2_ use, absorption and elimination. Although the reduction of CO_2_ absorption makes this new insufflation system an attractive alternative to standard insufflation systems, to the best of our knowledge, no randomized clinical studies have been performed which characterize the potential benefits and advantages in order to demonstrate significant clinical findings until now.

## Methods/Design

### Objectives and hypotheses

The primary objective of the present randomized trial is to investigate the mean operative time and to study the frequency and intensity of postoperative shoulder pain in patients undergoing laparoscopic cholecystectomy, colorectal surgery, and hernia repair with AirSeal™ (group A) compared with a standard pressure CO_2_ insufflator (group S).

The first primary endpoint will be whether the time of surgery in group A is more than or equal to the time of surgery in group S (H0_PE1_) or whether the time of surgery in group A is less than the time of surgery in group S (H1_PE1_).

The second primary endpoint will be whether shoulder pain in group A is more than or equal to shoulder pain in group S (H0_PE2_) or whether shoulder pain in group A is less than shoulder pain in group S (H1_PE2_).

### Study population and location

The study population will consist of patients undergoing elective laparoscopic cholecystectomy, colorectal surgery and hernia repair. A clinical evaluation and pre-randomization assessment must be completed for every patient, including a review of the eligibility criteria, signed and dated informed consent, inquiry of relevant past medical history and anesthesiological preoperative assessment including American Society of Anesthesiologists (ASA) class. Dropout criteria will be if patients recruited for laparoscopic resection are converted to an open procedure. Detailed eligibility criteria are listed in Table 1.

**Table 1 T1:** Eligibility criteria

**Inclusion criteria**	**Exclusion criteria**
• Aged 18 years and over	• Previous extensive abdominal surgery
• ASA ≤ 3	• Acute surgical intervention
• Informed consent provided	• Immunological dysfunctions like advanced liver disease, HIV or hepatitis C virus infection
• Diseases of the gallbladder, colon or hernias treated with elective laparoscopic procedure	• Pregnancy and lactation

Patients who meet the eligibility criteria will be given a patient information sheet and time to consider the trial. If interested, informed consent will be obtained for each patient prior to randomization. All personal information obtained for the study will be held securely and treated as strictly confidential.

This single centre trial will be performed at a high volume institution with experience in laparoscopic surgery (Department of General and Visceral Surgery, Sisters of Charity Hospital Linz, Austria). The clinical study centre of the surgical department will conduct this trial.

### Study design and randomization

After screening for eligibility is performed and informed consent is obtained, patients will be randomly stratified regarding type of operation in a 1:1 ratio into one of the following study arms: laparoscopic surgery with an AirSeal™ CO_2_ pressure insufflator (Surgiquest Inc., Milford, USA) (group A, experimental arm) or laparoscopic surgery with a standard CO_2_ pressure insufflator (Olympus America Inc. UHI-3, Center Valley, PA, US) (group S, control arm).

Patients are randomized using a web-based, central randomization and registration system. Treatment according to randomization (operation with AirSeal™ or standard CO_2_ pressure pneumoperitoneum) must be carried out within 14 days after randomization. For the study flow of the trial according to CONSORT guidelines, please see Additional file 1.

### Primary endpoints

Operation time, defined as the time from skin incision to closure of wound in minutes, is routinely documented in our operation program and will be evaluated after the operation by a newly designed survey. Postoperative shoulder pain will be assessed within 48 hours after the operation using the visual analogue pain scale (VAS). Postoperative pain will be assessed in a double-blinded manner, neither the patient, the assessor of shoulder pain, nor the postoperative caregivers will be aware of the technique to which the patient will been randomized.

### Secondary endpoints

Blood sample remains will be collected during routinely preformed venepuncture prior to surgery, intraoperatively after pneumoperitoneum skin incision, after skin suture and 24 hours postoperatively. They will be kept and used for immunological evaluation. All routine laboratory diagnostics will be performed immediately after blood collection. For the determination of the target parameters the EDTA (Ethylenediaminetetraacetic acid) plasma must be frozen by -80°C. All interleukins and cytokines will be measured at the end of patient recruitment in one sequence. Blood gas analysis and documentation of the ventilation volume will be performed. This intraoperative data will be also collected by the survey. Analgetic requirements, wound infections, anastomotic leakage and postoperative hemorrhage of all the patients in the postoperative period and length of hospital stay will be also recorded.

The immunological aspects will be: changes in the concentration of certain cytokines and angiogenic factors serum levels in the early postoperative period, and target parameters (soluble interleukin-1 receptor family member ST2 (sST2), interleukin (IL)-6, IL-8, IL-10, vascular endothelial growth factor A (VEGF-A) and endostatin).

The anesthesiological aspects will be: tidal volume, positive end expiratory pressure (PEEP), peak pressure, respiratory minute volume, acid–base balance and CO_2_ elimination in the patients, measured before insufflation, during surgery and after deflation of the pneumoperitoneum.

### Operative procedure

All patients will be anesthetized following a strict protocol for premedication, anaesthesia and intubation as well as mechanical ventilation and monitoring for CO_2_ level. The operation will be performed by experienced staff surgeons involved in the study. In all patients, access will be achieved using four working ports and the same instruments. In group A, one 5 mm AirSeal™ access port will be used instead of one standard 5 mm port. Pneumoperitoneum will be created without a visual control using a Veress needle (Ethicon Endo Surgery Inc., Cincinnati, US) for insertion through a small skin incision in the umbilical region. Intraperitoneal pressure using CO_2_ gas should be kept at around 12 mmHg. The patient should be placed in a reverse Trendelenburg position with left side down. Residual CO_2_ pneumoperitoneum will be evacuated at the end of the procedure by compressing the abdomen whilst taking care to keep the valve of the trocar open.

### Data collection

Daily visits with study patients will be done by the clinical investigator to collect information on primary and secondary outcome parameters. A detailed database will be collected, including sex, age and body mass index (BMI), ASA grade, medical history prior to operation, quality of surgical field exposure, duration of surgery and postoperative shoulder and other pain VAS score. The number of intravenous and oral medications required, use of drainage and other intraoperative and postoperative events in all patients will be recorded as well as length of hospital stay. All routine blood parameters and blood gas analysis data will be saved. Table 2 summarizes the course of examination and data collection process.

**Table 2 T2:** Course of examination

**Visit**	**Screening visit**	**At skin incision (pneumoperitoneum insufflation)**	**At skin suture (pneumoperitoneum deflation)**	**Daily postoperative ward visits**	**At discharge**
Past and current medical history	x				
Preanesthesia evaluation	x				
Physical examination and personal data (height, weight, age, ASA)	x				
Randomization	x				
Blood draw and frozen sample	x	x	x	x	
Blood gas draw		x	x		
VAS shoulder pain				x	
Postoperative complications (wound infections, intra-abdominal abscess and anastomotic leakage)				x	x

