### Sample size estimation

On the basis of a comparison of two proportions, a sample size of 182 (n = 91 per group) is needed to have 80% power at a 5% significance level, assuming a dropout rate of 5%.

Data, assumptions and conditions are: type I error (2.5% one-sided), type II error (20%), non-parametric test (Mann–Whitney *U*-test), n (group A): n (group S) (ratio of 1:1) and per-protocol analysis:

(1)$$\begin{array}{l} \mathrm{group}\;A\;\left(\mathrm{mean}\;\pm \;\mathrm{standard}\;\mathrm{deviation}\right):\;74,8\;\pm \;41,3\;\min\\ \mathrm{group}\;S\;\left(\mathrm{mean}\;\pm \;\mathrm{standard}\;\mathrm{deviation}\right):\;93,5\;\pm \;41,3\;\min \end{array}\;\}\Delta =20\%$$

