### Statistical methods

The estimation of effect size for selected variables will be the calculation of two-sided 95% confidence intervals.

Primary endpoint one will be set due to the clear duration difference between colorectal surgery and the other types of surgery (laparoscopic cholecystectomy and laparoscopic hernia repair) a normal distribution of the data can be excluded. Therefore, a nonparametric test, namely the exact Mann–Whitney *U*-test will be used (type I error = 2.5% one-sided).

Primary endpoint two (only if H0_PE1_ is rejected), will be set by checking data sets for normal distribution (test of normality: Kolmogorov-Smirnov with Lilliefors significance correction, type I error = 5%). In the case of normal distribution the *t*-test for independent samples with correction for heteroscedasticity (Levene’s test, type I error = 5%) will be applied. In the case of a significant deviation from the normal distribution the exact Mann–Whitney *U* test will be used instead. In both cases the type I error will be 2.5% one sided.

Metric variables data sets will be checked for normal distribution (test of normality: Kolmogorov-Smirnov with Lilliefors significance correction, type I error = 5%). Normally distributed data sets will be compared between the groups by the *t*-test for independent samples with correction for heteroscedasticity (Levene’s test, type I error = 5%). If there is a significant deviation from the normal distribution the exact Mann–Whitney *U* test will be used instead.

Ordinal variables will be checked by the exact Mann–Whitney *U* test and nominal variables by the exact chi-square homogeneity test or, for 2 × 2 frequency tables the Fisher's exact test.

All tests will be two-sided with a confidence level of 95% (*P* <0.05). As no adjustment of the *P* values will be made, the resulting *P* values will only be descriptive.

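### Both primary tests are unadjusted two-sample tests although age, sex, BMI and ASA grade are collected before surgery; they are valid, but some precision may be left unused

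*Protocol article*

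**What the plan says.** Under Data collection: "A detailed database will be collected, including sex, age and body mass index (BMI), ASA grade, medical history prior to operation". Table 2 places height, weight, age and ASA at the screening visit. Sex is named only in the text, but it too is fixed before surgery.

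Under Statistical methods, operation time is tested without covariates: "Therefore, a nonparametric test, namely the exact Mann–Whitney" U-test, one-sided at 2.5%. Shoulder pain is tested only if the first null hypothesis is rejected. A normality test then chooses between a t-test and a rank test: "In the case of a significant deviation from the normal distribution the exact Mann–Whitney" U-test is used. No patient characteristic and no stratum term appears in either comparison.

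Study design and randomization says that "patients will be randomly stratified regarding type of operation in a 1:1 ratio". Sample size estimation uses the same kind of unadjusted test: "type I error (2.5% one-sided), type II error (20%), non-parametric test (Mann–Whitney" U-test), and concludes that "a sample size of 182 (n = 91 per group) is needed". By Sample size estimation and Analysis populations, the efficacy analysis is per protocol.

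**The concern.** A covariate measured before treatment that predicts the outcome can be used to remove explainable variation from a randomised comparison. Four such candidates are already scheduled for collection and vary within each type of operation, yet the plan names tests that cannot use them. This is a stated choice of test, so it is not a detail that a condensed article merely omits.

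What is at stake is efficiency. Power for operation time matters twice, because it also decides whether shoulder pain is tested confirmatorily at all. Shoulder pain has no baseline value in Table 2, so these covariates and operation type are among the few adjusters available for it. Fixing the list in advance would also rule out choosing covariates after seeing the data.

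**Working it through.** **1. Does the planned power rely on adjustment?** Inputs from Sample size estimation: means 74.8 and 93.5 min, SD 41.3 min, 2.5% one-sided, 80% power, 5% dropout.

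- Standardised difference: (93.5 − 74.8)/41.3 = 18.7/41.3 = 0.453.
- Noether's formula for the Mann–Whitney test: N = (1.960 + 0.842)² / [3(p − 0.5)²], with p = Φ(0.453/√2) = 0.6256. This gives N = 165.9, or 83 per arm. Dividing by 0.95 gives 88 per arm, 176 in total.
- With the difference rounded to 0.45: 84 per arm, 89 after dropout, 178 in total. This is within 3% of the stated 182.
- Power at 86 evaluable per arm (91 × 0.95): Φ(√(3 × 172) × 0.1256 − 1.960) = 81.4%.

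The stated size is therefore consistent with an unadjusted rank test. The section's reference to two proportions cannot be reproduced, since no proportions are given, and it is not used here.

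**2. What could the covariates add?** The documents give no R², so a range is assumed. Replacing the SD by SD × √(1 − R²) in the calculation above, with 86 per arm and no cost for estimating slopes:

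| Assumed R² | Power | SE reduction |
|---|---|---|
| 0 | 81.4% | 0 |
| 0.02 | 82.1% | 1% |
| 0.05 | 83.3% | 2.5% |
| 0.10 | 85.1% | 5% |

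These are idealised upper figures.

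**3. Net of the cost of fitting.** This was simulated with 172 evaluable patients, three operation types, normal outcomes and four independent covariates. Outcomes are ranked within type and regressed on the covariates without arm, and the residuals are compared within type. With slopes common to all types, the change relative to stratification alone is about:

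| Assumed within-type R² | Change in power (percentage points) |
|---|---|
| 0% | −1 to 0 |
| 5% | +1 |
| 10% | +1 to +3 |
| 15% | +3 |

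At 15% another run gave up to +5; the lower figure is used here. One-sided type I error stayed at about 2.2–2.7%, against a nominal 2.5%.

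Fitting separate slopes in each operation type uses 3 × 4 = 12 slopes instead of four. It loses about 1 to 4 power points when R² is 5% or less.

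**4. Operation type for comparison.** Statistical methods itself says that colorectal operations clearly differ in duration from the other two. A simulation assumed one third colorectal, 86 per arm, and that type explains a given share of the variance in operation time:

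| Share due to type | Unadjusted power | Stratified power | Type I error, unadjusted |
|---|---|---|---|
| 0 | 81% | 81% | about 2.2% |
| 0.2 | 85% | 90% | 1.6% |
| 0.4 | 87% | 96% | 0.5% |

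The stratified (van Elteren) test stayed near 2.3–2.5%. Ignoring the stratum is conservative. Stratification is probably the larger gain for operation time.

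**5. Shoulder pain.** No SD, effect size or predictor is given, so no figure can be calculated.

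**The case against.** The strongest objection is that nothing here is wrong. A two-group test in a randomised trial is valid, the sample size was planned for that test, and the planned power is met without adjustment. That stands in full.

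Three stronger readings are tempting, and the documents do not support them.

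- *The trial is discarding precision it already has.* No section says that age, sex, BMI or ASA predicts operation time or shoulder pain. If they do not, nothing is lost. Operation type is the only predictor the protocol names.
- *Chance imbalance in BMI or ASA distorts the result.* The type I error of a randomised comparison already allows for chance imbalance, as far as the per-protocol exclusions are unrelated to arm.
- *Adjustment raises the planned 80% to about 80.8%, 82.0%, 84.0% or 86.0% at R² of 2%, 5%, 10% or 15%.* This follows from Φ(2.802/√(1 − R²) − 1.960). But it applies a within-type R² to a power planned for an unadjusted test on the overall SD, and it ignores the cost of fitting. If stratification already brings power to 90% or 96%, the same formula adds only about 0.6 to 4.0 points (90.6–94.0%) or 0.3 to 2.1 points (96.3–98.1%). The efficacy analysis also has about 182 × 0.95 = 173 patients, not 182.

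It can also be said that these covariates are secondary to operation type. That is right, so the adjustment should accompany stratification and not replace it. It does not make the covariates redundant, because they vary within operation type.

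**Conclusion.** The point holds as a low-severity efficiency recommendation. Both primary tests are unadjusted, the four covariates are scheduled before surgery, and a prespecified adjustment would be valid. For operation time, the change beyond stratification lies between a loss of up to about one power point (covariates not prognostic) and a gain of about three (15% of within-type variation explained). For shoulder pain the size is unknown.

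This rests on assumed R² values, on normal outcomes and independent covariates in the simulation, on an assumed mix of operation types, and on the covariates being essentially complete, which is inferred from the collection schedule.

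**What to change.** In Statistical methods, state that both primary comparisons are stratified by operation type and adjusted for a list fixed now: age, sex, BMI and ASA grade as one ordered score.

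- *Rank-based analysis:* rank the outcome within operation type; regress the ranks on the four covariates with slopes common to all types and without arm; compare the residuals between arms by permutation within type, one-sided at 2.5%.
- *Mean-based analysis:* fit a model with arm, operation type and the same four covariates.
- *Sensitivity analysis:* keep the unadjusted tests now specified.

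The wording should exclude separate regressions by operation type, which can lose power.

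No new data are needed. The cost is a few lines of text and code, about four degrees of freedom, up to about one power point if the covariates turn out not to be prognostic, and a short amendment. Under Ethical considerations that amendment needs ethics committee approval. It should be settled before outcomes are compared by arm; Trial status expects recruitment to end by March 2014.
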